### Interventions

Take5 was designed to be implemented as a universal tool for all parents who attend their child’s medical procedure, to increase parental psychological coping and associated behaviours, to target the child’s procedural coping. Given the acute delivery design, Take5 was intentionally brief to be provided via a tablet in a clinical environment on the day of surgery prior to the procedure.

Specifically, Take5 communicated three key messages: What to expect during the patient journey (procedural preparation), the benefits of distraction to the child (reinforcing parental behaviour), and psychoeducation to provide general coping strategies for the parent to manage personal distress during and after the child’s procedure. Procedural preparation was communicated because patients and parents commonly express unmet expectations for information [33]. Positive behavioural reinforcement was used because fear-based messaging is thought to have unintentional consequences [34]. The psychoeducation was modelled on Acceptance Commitment Therapy to assist with normalising feelings of distress for parents [22]. An acceptability and feasibility study (unpublished) of 10 parents receiving Take5 demonstrated good acceptability, and increased positive parenting behaviours, and reduced child procedural distress, compared to data from Brown et al.’s observational study [28].

The ‘Take5’ video was adapted by the authors (a group of psychologists and anaesthesiologists) for anaesthetic induction. The authors initially consulted the hospital’s consumer panel of parents to understand what preparatory information parents valued regarding the anaesthetic induction, what helped their child have a positive medical experience, and what advice they had for parents to cope while supporting their child. The panel feedback was documented, thematically summarised, and agreed by the authors as in or out of scope for the video. In-scope feedback pertained to the key messages and generalisability to other hospital locations. Using the in-scope panel feedback, the authors adapted the procedural preparation, parental behaviour and psychoeducation components of Take5 to ensure appropriate for anaesthetic induction. The authors presented a drafted video script back to the consumer panel for validation and further feedback. The panel provided positive comments on the script and suggestions for the animation.

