### Outcomes

The primary outcome of the study is child peri-operative anxiety as measured by the modified Yale Preoperative Anxiety Scale Short Form (mYPAS-SF) [35], the Peri-operative Adult–Child Behavior Interaction Scale (PACBIS) [36], the Visual Analogue Scale for Anxiety (VAS-A) [37], and the Induction Compliance Checklist (ICC) [38].

The secondary outcomes include:Child post-operative pain measured during recovery via observation using the Face, Legs, Activity, Cry and Consolability Pain Scale (FLACC) [39];Child emergence delirium scored during recovery using the Cornell Assessment for Paediatric Delirium (CAP-D) [40];Parent satisfaction with procedure via a purpose-built survey of feedback via a numeric rating scale (1–10 of increasing satisfaction);Parent and child 3-month psychosocial outcomes: measured using validated measures of adult psychological well-being, specifically the Depression, Anxiety and Stress Scale (DASS-21) [41], child physical, mental and social health the Patient-Reported Outcomes Measurement Information System (PROMIS [42] and PROMIS Early Childhood [43]) and health-related quality of life using the Child Health Utility instrument (CHU9D) [44];Acceptability: A semi-structured interview developed in specifically for the ‘Take5’ video will assess acceptability of delivery and content of ‘Take5’; andCost-effectiveness via the cost of intervention, and direct and indirect healthcare costs to the healthcare system.

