### Participant timeline

Enrolment and consenting of participants occur when parents and child (patient) arrive on their day of surgery, have been placed in the holding bay and are deemed eligible for the study. The holding bay is where patients wait after being admitted into the hospital, and receive a medical check by nurses and doctors to ensure they are fit and ready for surgery. This pre-operative environment is a busy clinical setting and parents are approached after all clinical checks have been conducted and the anaesthetist has confirmed to the research team whether pre-medication will be given (part of exclusion criteria). Parents of patients who will not receive pre-medication are approached for recruitment.

Time period 1 (t1) is defined as time at the holding bay after the family has been enrolled in the study and allocated to a study condition. At this time, the intervention group are the provided with the Take5 video in addition to standard care. This will occur approximately 15 min prior to surgery. Comparatively, the control will only experience standard care. The anaesthetist and research team aim to provide sufficient time for parents to watch the video and process the information prior to anaesthetic induction. Parents of both groups are asked their levels of anxiety measured by the VAS-A, however, parents in the intervention group will be asked after watching the Take5 video. The child’s anxiety will be observed by the researcher using the mYPAS-SF scale and parent-reported measured by the VAS-A. Parent and child behaviours at this time are observed measured by the PACBIS. When the surgical team are ready, the parent and child will be escorted from the holding bay into the induction theatre.

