Time period 2 (t2) is defined as from when the parent and child is inside the induction theatre and when the anaesthetist commences the induction procedure, until the child is fully anaesthetised. Procedural commencement may involve the anaesthetist engaging the child with non-procedural talk, helping the child get on the bed, offering the mask to the child or beginning the intravenous preparation. This time period is expected to be 3–10 min in length. During this time, video recording and capturing of observation data occurs, including parent–child behaviours measured by the PACBIS, child’s anxiety measured by the mYPAS-SF, and child’s cooperation measured by the ICC. After the child is fully anaesthetised and the parent leaves the theatre, the parent will be asked to rate their own and child's level of anxiety during the induction, as well as their current (post-induction) level of anxiety, measured by the VAS-A.

Time period 3 (t3) is defined as when the child regains consciousness (general anaesthesia wears off) after the procedure. At this point, clinical staff will score the child for emergence delirium measured by the CAP-D and pain measured by the FLACC.

Time period 4 (t4) is defined as approximately day 92 (i.e. 3 months post discharge) after the child’s surgery where the participating parent will be asked to self-report anxiety and depression symptoms measured by the DASS-21 and provide a proxy-report for the child's physical, mental and social health measured by the PROMIS and health-related quality of life measured by the CHU9D.

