### Recruitment

The clinical research assistant (social worker with psychology training) will perform recruitment, obtain written informed consent, provide the Take5 video intervention as per randomisation through sealed envelopes, video record the anaesthetic induction and undertake data collection. All participant data will be scored under interrater reliability by another member of the research team blinded to group allocation.

Patients who are scheduled for elective surgery will be screened for eligibility by a trained research assistant daily (weekdays) by reviewing the elective surgery list. Eligibility for the study will be confirmed with the rostered consultant anaesthetist. Participants who meet eligibility criteria will be approached to participate by the research assistant while at the Holding Bay on the day of surgery prior to receiving the anaesthetic induction. If the research assistant considers the parent to be under significant psychological distress some normalisation of the experience and follow up care will be provided to the participant as part of duty of care. A record of all patients screened exclusion criteria and reason for refusal will be recorded by the research assistant.

Recruited parents will be asked to report the levels of anxiety for themselves (parent) and their child. Parents allocated to the control group will be asked prior to the anaesthetic induction, whereas parents in the intervention group be asked after receiving the video intervention. Both groups will be filmed during their anaesthetic induction and parents will be asked to report their own and their child's anxiety levels during and after induction, and their own satisfaction level with the anaesthetic induction experience. Care will be taken to ensure the filming is unobtrusive and will not increase the child’s or parent’s anxiety. All participants will receive questionnaires after 3 months post-surgery to follow up on their mental and physical outcomes.

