#### Concealment mechanism

The envelopes will be prepared by a third-party separate to the trial; however, masking the research assistant, patient and their parent to the treatment allocation will not be possible.

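### The child's VAS-A, listed as a primary-outcome measure in one section only, is a proxy rating by the unmasked parent who received the video, so it should not carry the child-anxiety claim

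*Protocol article*

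**What the plan says.** The Outcomes section of the protocol article opens: "The primary outcome of the study is child peri-operative anxiety as measured by" four instruments, namely the mYPAS-SF, the PACBIS, "the Visual Analogue Scale for Anxiety (VAS-A) [37], and the Induction Compliance Checklist (ICC) [38".

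The Participant timeline says who scores the VAS-A for the child. At t1, in the holding bay: "The child’s anxiety will be observed by the researcher using the mYPAS-SF scale and parent-reported measured by the VAS-A". At t2: "After the child is fully anaesthetised and the parent leaves the theatre, the parent will be asked to rate their own and" the child's anxiety during the induction. The Recruitment section covers the parent's ratings of self and child together. Control parents are asked before induction, "whereas parents in the intervention group be asked after receiving the video intervention". No rating before the video is described.

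The rater is the person treated. Trial design and Interventions say that the video goes to parents and is meant to improve their coping, with psychoeducation "to assist with normalising feelings of distress for parents". The Concealment mechanism section states that "masking the research assistant, patient and their parent to the treatment allocation will not be possible".

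Blinded scoring is described for the filmed induction. Blinding, Data collection and methods, and Statistical methods have a second, blinded researcher score the behavioural measures, and the last names the mYPAS-SF, PACBIS and ICC. The VAS-A is not among them.

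Two other places give a different primary outcome. The Sample size section defines it as the mYPAS-SF at induction and sizes the trial on that scale alone. The abstract lists the mYPAS-SF, PACBIS and ICC, without the VAS-A.

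**The concern.** Parent report in an open trial is common, and masking parents here is impossible. What is particular to this trial is that the intervention is designed to change the emotional state of the person who then scores the child. A parent who has just been told that distress is normal and what to expect may give the same child a different score. The measure cannot tell that apart from a change in the child.

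This would be unremarkable for a labelled secondary outcome. It matters because the Outcomes section places the rating among the measures of the primary outcome. Read literally, a VAS-A difference could support a claim of reduced child anxiety while the blinded scales show nothing. One primary hypothesis concerns anxiety that children report, yet the timeline contains no child self-report. The parent's rating is the only reported measure of child anxiety, so that hypothesis appears to rest on it (an inference). The cost-effectiveness analysis takes its effects from the primary outcomes of behaviour and anxiety without naming an instrument, so the text does not exclude the child VAS-A there either.

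**Working it through.** **Step 1. Status of the VAS-A as a measure of child anxiety**

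| Place in the protocol article | Primary outcome measured by | VAS-A included? |
|---|---|---|
| Abstract, Methods | mYPAS-SF, PACBIS, ICC | No |
| Outcomes | mYPAS-SF, PACBIS, VAS-A, ICC | Yes |
| Sample size | mYPAS-SF at induction | No |

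The three statements cannot all hold. Only Outcomes gives the VAS-A primary status.

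**Step 2. Who scores, and what protects the score**

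| Measure | Scored by | Blinded scoring described? |
|---|---|---|
| mYPAS-SF, PACBIS, ICC at induction | Two researchers, from film for the blinded one | Yes |
| Child VAS-A, t1 and t2 | Parent, after the video in the Take5 arm | No, and not possible |
| Parent's own VAS-A | Parent, about self | No; self-report of a different construct |

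Filming covers the induction only. That is why the protected measure is the mYPAS-SF at induction, not at t1.

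**Step 3. The plan's own power figure**

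Inputs from Sample size: difference 55 − 40 = 15 points, effect size 0.61 (implied SD 15/0.61 = 24.6), n = 50 per group, α 0.05. With λ = d·√(n/2) = 0.61 × √25 = 3.05:

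- two-sided: Φ(3.05 − 1.960) = 0.862 (noncentral t, 98 df: 0.855);
- one-sided: Φ(3.05 − 1.645) = 0.920 (noncentral t: 0.917).

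The stated power above 90% is reached with a one-sided 5% test and not with a two-sided one; the article does not state sidedness. The present point does not depend on this.

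**Step 4. Illustration of a pure rating shift**

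Assume that child anxiety is identical in both arms and that Take5 parents score b SD lower for the same child. With n = 50 per arm, λ = b × √25 = 5b. The chance of p < 0.05 at the two-sided 5% level is approximately Φ(5b − 1.960) + Φ(−5b − 1.960).

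| b (SD) | λ | Normal approximation | Noncentral t, 98 df |
|---|---|---|---|
| 0 | 0 | 5.0% | 5.0% |
| 0.1 | 0.5 | 7.9% | 7.9% |
| 0.2 | 1.0 | 17.0% | 16.8% |
| 0.3 | 1.5 | 32.3% | 31.8% |
| 0.5 | 2.5 | 70.5% | 69.7% |

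The values of b are assumptions. A shift in the other direction of the same size would give the same rejection rates, but against Take5.

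**The case against.** The strongest reply is that the VAS-A is not really primary. The trial is sized on the mYPAS-SF, the abstract omits the VAS-A, and once Outcomes agrees with Sample size most of the difficulty goes. The VAS-A may also be in the list for parent anxiety: the abstract names parent anxiety as primary, a primary hypothesis concerns it, and the VAS-A is the only instrument that records the parent's own anxiety. Both points have force. But Outcomes expressly ties the list to the child's anxiety, and reconciling the sections is the remedy, not a reason to leave them.

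It can also be said that the table of rejection rates is just the power of a t-test for an assumed shift, that 0.5 SD is close to the full design effect of 0.61, and that a parent told what to look for might notice more distress, not less. All of that stands. The passages linking parent and child emotion describe a real route by which a calmer parent may calm a child; they are not evidence of rating bias.

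A reader might go further than the article allows in three ways:

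- *The trial's main result is compromised.* It is not. The induction mYPAS-SF has blinded video scoring, and a VAS-A difference without a matching difference on the observed scales would be visible.
- *The cost-effectiveness analysis will use the child VAS-A.* Statistical methods names no instrument for anxiety, so this is possible but not stated.
- *The way the VAS-A is collected adds bias, or the parent's own VAS-A is misused.* The article does not say whether parents mark the scale themselves, and the forms are in an additional file not shown. Nowhere is the parent's own VAS-A used for a claim about the child.

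**Conclusion.** The point holds, confined to one measure. Outcomes lists as a measure of the child's anxiety a rating that the unmasked, treated parent makes and that no blinded coding can protect. It does so in conflict with Sample size and the abstract. A difference on the child VAS-A cannot separate a change in the child from a change in the rater.

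This conclusion rests on the stated rater, timing and masking, not on the arithmetic. How often a false claim would follow is unknown: about 8% to 70% for assumed shifts of 0.1 to 0.5 SD, against a nominal 5%, with both size and direction assumed. The change should be made, because a blinded measure of the same construct is already collected and already used for sizing.

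**What to change.** - **Outcomes:** bring the section into line with Sample size by making the mYPAS-SF at induction, as scored from video by the blinded coder, the basis of the child-anxiety claim. List the child VAS-A as a secondary outcome labelled as an unmasked parent proxy rating.
- **Statistical methods:** state that the child-anxiety effect in the cost-effectiveness analysis is that blinded mYPAS-SF.
- **Leave as it is:** the parent's own VAS-A, as the self-report measure for the parent-anxiety hypothesis, and the way the VAS-A is collected.

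The cost is one fewer measure that can be called primary, plus an outcome amendment. Under the Harms section, an important change to outcomes goes to the investigators, ethics committees, information and consent forms, registry and journal. It should be made before unblinded results are seen. It needs no extra participants, staff or procedures, and because data collection does not change it can be made with recruitment under way.

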### Participant timeline

Enrolment and consenting of participants occur when parents and child (patient) arrive on their day of surgery, have been placed in the holding bay and are deemed eligible for the study. The holding bay is where patients wait after being admitted into the hospital, and receive a medical check by nurses and doctors to ensure they are fit and ready for surgery. This pre-operative environment is a busy clinical setting and parents are approached after all clinical checks have been conducted and the anaesthetist has confirmed to the research team whether pre-medication will be given (part of exclusion criteria). Parents of patients who will not receive pre-medication are approached for recruitment.

Time period 1 (t1) is defined as time at the holding bay after the family has been enrolled in the study and allocated to a study condition. At this time, the intervention group are the provided with the Take5 video in addition to standard care. This will occur approximately 15 min prior to surgery. Comparatively, the control will only experience standard care. The anaesthetist and research team aim to provide sufficient time for parents to watch the video and process the information prior to anaesthetic induction. Parents of both groups are asked their levels of anxiety measured by the VAS-A, however, parents in the intervention group will be asked after watching the Take5 video. The child’s anxiety will be observed by the researcher using the mYPAS-SF scale and parent-reported measured by the VAS-A. Parent and child behaviours at this time are observed measured by the PACBIS. When the surgical team are ready, the parent and child will be escorted from the holding bay into the induction theatre.

Time period 2 (t2) is defined as from when the parent and child is inside the induction theatre and when the anaesthetist commences the induction procedure, until the child is fully anaesthetised. Procedural commencement may involve the anaesthetist engaging the child with non-procedural talk, helping the child get on the bed, offering the mask to the child or beginning the intravenous preparation. This time period is expected to be 3–10 min in length. During this time, video recording and capturing of observation data occurs, including parent–child behaviours measured by the PACBIS, child’s anxiety measured by the mYPAS-SF, and child’s cooperation measured by the ICC. After the child is fully anaesthetised and the parent leaves the theatre, the parent will be asked to rate their own and child's level of anxiety during the induction, as well as their current (post-induction) level of anxiety, measured by the VAS-A.

Time period 3 (t3) is defined as when the child regains consciousness (general anaesthesia wears off) after the procedure. At this point, clinical staff will score the child for emergence delirium measured by the CAP-D and pain measured by the FLACC.

Time period 4 (t4) is defined as approximately day 92 (i.e. 3 months post discharge) after the child’s surgery where the participating parent will be asked to self-report anxiety and depression symptoms measured by the DASS-21 and provide a proxy-report for the child's physical, mental and social health measured by the PROMIS and health-related quality of life measured by the CHU9D.

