#### Blinding

Clinical staff (anaesthetic doctors and nurses) will be blinded to the treatment allocation. As induction will be filmed, the researcher responsible for coding the behavioural measures will also be blinded to treatment allocation.

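### Anaesthetic staff are declared blinded, yet after allocation the anaesthetist helps make time for a video that only Take5 parents watch, so staff can learn the arm

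*Protocol article*

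**What the plan says.** The Blinding section of the protocol article makes an unqualified claim: "Clinical staff (anaesthetic doctors and nurses) will be blinded to the treatment allocation". It adds that the researcher who codes behaviour from the induction film is also blinded.

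The Participant timeline defines t1 as time in the holding bay after enrolment and allocation. Take5 parents are shown the video at this point, and the article says of the timing: "This will occur approximately 15 min prior to surgery". For the other arm it says: "Comparatively, the control will only experience standard care". The next sentence is the one at issue: "The anaesthetist and research team aim to provide sufficient time for parents to watch the video and process the information prior to anaesthetic induction".

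At t2 the parent and child are in the induction theatre, and the period runs from "when the anaesthetist commences the induction procedure, until the child is fully anaesthetised". At t3, in recovery, "clinical staff will score the child for emergence delirium measured by the CAP-D and pain measured by the FLACC".

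The Concealment mechanism section concedes that "masking the research assistant, patient and their parent to the treatment allocation will not be possible".

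**The concern.** Staff blinding does two jobs in this trial, and the stated procedure weakens both.

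First, the anaesthetist is part of what happens to the child at induction. The timeline counts the anaesthetist's non-procedural talk, help in getting onto the bed and offer of the mask as part of the start of the procedure. An anaesthetist who knows that the parent has been coached may distract more, step back more, or pace things differently. That would be a real change in the conditions under which mYPAS-SF, PACBIS and ICC are observed. It could not be separated from the effect of the video.

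Second, CAP-D and FLACC are observer-rated and are scored by clinical staff. If the scorers know the arm, expectation can enter the rating directly.

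If the blinding claim stands as published, readers will treat care during induction and the recovery scores as protected from both effects.

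**Working it through.** There is no figure to reproduce. The check sets the statements side by side and follows the possible routes by which staff could learn the arm.

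1. **Who is said to be blind.** Anaesthetic doctors and nurses, with no exception (Blinding).

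2. **What the anaesthetist does after allocation.** The sentence on making time belongs to t1, which begins once the family has been allocated. It gives the anaesthetist, jointly with the research team, the aim that the video can be watched and absorbed before induction.

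3. **Whether that activity is specific to one arm.** Yes. Controls get standard care alone at t1. Read literally, the sentence has a blinded person accommodating something that exists in one arm only.

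4. **Whether anything in the text makes it arm-neutral.** The article does not say that the same interval is kept for every enrolled family, that it is agreed before the envelope is opened, or that the arm is kept from staff in some other way.

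5. **Other routes.**
   - The video is given on a tablet in a clinical environment (Interventions). The place is the holding bay, which the timeline describes as a busy clinical setting.
   - The anaesthetist has confirmed eligibility and pre-medication status (Recruitment; Participant timeline), and so can know which children may be enrolled.
   - The parent and child know the arm and go into the induction theatre. No request that they keep it to themselves is described.

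6. **What the blinded second scorer protects.** Filming covers the induction. Statistical methods describes two researchers independently scoring each induction for mYPAS-SF, PACBIS and ICC. This guards the rating of those measures. It does not guard against a real change in how staff behaved while the film was running.

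7. **What it does not reach.** Recovery is not filmed in any procedure described. The Recruitment section says generally that all participant data are scored by a second, blinded team member, but no recording is described that would let this happen for CAP-D and FLACC. Those two outcomes therefore depend on the blinding of the staff who score them.

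**The case against.** The strongest reply is that this is an ambiguity and not a strict contradiction. The anaesthetist could leave the same slot for every enrolled family without being told the arm, and a journal article often leaves such logistics to the full protocol. Parents are approached only after clinical checks are finished, so planned staff contact in the holding bay may be over before the video starts. Controls also have research contact at t1 (VAS-A questions and observation), so contact with the research assistant does not reveal the arm. The scoring of the filmed measures is protected.

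Much of this is fair. An equal slot would reconcile the two statements, but the article does not say that one is used. Nor would it deal with a tablet visible in the holding bay or an unmasked parent at induction. The point also does not rest on silence: the article makes a positive claim of blinding and describes a procedure that undercuts it.

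A reader might infer three stronger things that the documents do not support:

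- **Take5 families wait longer.** It is tempting to set the 5-minute video against the window of about 15 minutes (5/15, or one third) and call that extra delay. The article gives no waiting time by arm, and the video may fill time the family would spend waiting anyway. It mentions no request to hold a case; families move when the surgical team is ready.
- **The induction team scores recovery.** The article uses the term clinical staff in both places but does not say that they are the same people.
- **Recovery scores are compromised for all 100 children.** This would require every scorer to know the arm, and nothing in the article shows that.

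**Conclusion.** The point holds in a limited form. The blinding claim and the timeline do not fit together as written, and staff who conduct the induction can learn the arm. For the induction measures, the exposure is a possible change in staff behaviour over the expected 3–10 minutes, not biased coding of the film. For CAP-D and FLACC, the exposure is conditional: it arises if the recovery scorers learn the arm, and no second route to blinded scoring is described for them.

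The size and direction of any bias cannot be derived from the article. The conclusion rests on reading the sentence about making time in its place, after allocation and directly after the description of the control arm, and on no arm-neutral interval being stated. If the full protocol already fixes an equal interval and keeps the video out of staff sight, what remains is mainly a correction to the wording and the risk that a parent discloses the arm.

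**What to change.** Reword the sentence in the Participant timeline so that it applies to both arms. The same interval between enrolment and transfer to theatre is agreed with the anaesthetist for every enrolled family before the envelope is opened. The video is shown out of sight of clinical staff. Parents in both arms are asked not to mention their allocation to staff.

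If this cannot be done, qualify the statement in the Blinding section so that it does not claim blinded clinical staff without exception, and report CAP-D and FLACC as not reliably blinded. As recruitment began in June 2022, the report should also describe honestly how families already enrolled were handled.

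Matched tablet tasks for controls and recorded guesses of allocation are optional additions; the point does not depend on them.

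The cost is a few lines of protocol wording and a short request to parents. The downside is that control families may wait a few minutes in the holding bay, within the stated window of about 15 minutes.
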